## Abstract

**Background::**

Coronary heart disease (CHD) chronic heart failure has high morbidity and mortality, which poses a serious threat to patients’ quality of life and life safety. For the treatment of chronic heart failure of CHD, in addition to drugs, high quality nursing measures are also very important. Cluster nursing is a high-quality nursing model based on evidence-based evidence. There is no clinical study to evaluate the effect of cluster nursing on cardiac function and quality of life of CHD patients with chronic heart failure.

**Methods::**

This is a prospective randomized controlled trial to investigate the effects of cluster nursing on cardiac function and quality of life in patients with CHD chronic heart failure. Approved by the Clinical Research Ethics Committee of our hospital, patients will be randomly assigned to either routine nursing or cluster nursing. They will be followed up for 3 months after 4 weeks of treatment. Observation indicators include: The total effective rate of cardiac function improvement, Minnesota Living with Heart Failure Questionnaire, left ventricular ejection fraction, N-terminal pro-brain natriuretic peptide, 6-minute walk test, adverse reaction, etc. Data were analyzed using the statistical software package SPSS version 25.0.

**Discussion::**

This study will evaluate the effects of cluster nursing on cardiac function and quality of life of CHD patients with chronic heart failure. The results of this study will provide clinical basis for establishing reasonable and effective nursing programs for CHD patients with chronic heart failure.

## Introduction

1

With the changes in people's diet structure and life schedule, the incidence of cardiovascular diseases is increasing and it has become the deadliest disease in the world.^[1,2]^ Chronic heart failure is the terminal stage of the development of many cardiovascular diseases.^[3]^ According to the American epidemiological survey, there are currently 6 million patients with chronic heart failure in the United States, and this number is expected to increase to 9 million by 2030.^[4]^ At present, there has been no breakthrough in the treatment of coronary heart disease (CHD) complicated with chronic heart failure. Due to the particularity of the disease, the quality of life of patients is seriously reduced, and life is even endangered, causing huge burden to patients and their families.^[5]^ Therefore, how to improve the quality of life of patients, improve the state of cardiac function, and reduce the case fatality rate are the directions that clinical workers need to focus on.

The treatment of heart disease complicated with chronic heart failure cannot only rely on drugs, high-quality nursing work also plays an important role in the treatment.^[6]^ Studies have shown that patients with CHD complicated with heart failure can enhance their therapeutic effect and improve their quality of life on the basis of routine medication combined with quality nursing.^[7]^

Cluster nursing is an intensive care unit idea jointly proposed by the American Institute of Health and the Association of Volunteer Hospitals. It is a nursing program that integrates a series of evidence-based nursing interventions.^[8]^ Cluster nursing consists of 3 to 5 nursing measures with strong operability, simplicity, and easy acceptance in clinical practice, each of which has been verified by clinical practice and can effectively improve the symptoms of patients. Clinical observation shows that the synergistic effect of these interventions is better than that of a single measure.^[9]^ At present, cluster nursing has been applied to patients after surgery and intensive care unit, and has received positive feedback.^[10,11]^ However, there is still a lack of high-quality clinical studies to explore the impact of cluster nursing on patients with coronary heart failure. Therefore, this study will explore the effects of cluster nursing on cardiac function and quality of life in CHD patients with chronic heart failure.

## Materials and methods

2

### Study design

2.1

This is a prospective randomized controlled trial to study the effects of cluster nursing on cardiac function and quality of life of CHD patients with chronic heart failure. This study will follow Consolidated Standards of Reporting Trials,^[12]^ and the flow chart is shown in Figure 1.

**Figure 1 F1:**
[figure not shown]
Flow diagram.

### Ethics and registration

2.2

This research scheme is in line with the Helsinki Declaration and approved by the Clinical Research Ethics Committee of our hospital. This experiment is registered in the open science framework (registration number: DOI 10.17605/OSF.IO/WQMNJ). Before being randomly divided into groups, all patients need to sign a written informed consent form, and they are free to choose whether or not to continue the trial at any time.

### Sample size

2.3

The calculation of sample size is based on mean and standard deviation of scores of Minnesota Living with Heart Failure Questionnaire^[13]^ after treatment. According to the results of the pilot study, the observation group will be 27.91 ± 4.31, and the control group will be 31.12 ± 4.85. Set α = 0.025, unilateral test, β = 0.20. According to the calculation of PASS15.0 software, 34 participants are needed in each group, the estimated withdrawal rate is 10%, so that 38 participants will be included in each group.

### Patients

2.4

Inclusion criteria: ① Patients with occlusive myocardial infarction who meet the diagnostic criteria for CHD, which the stenosis rate of at least one of the main coronary arteries is more than 50%; ② Patients who are in line with the diagnostic criteria of chronic heart failure,^[14,15]^ and Doppler ultrasound suggests that left ventricular ejection fraction <50%. ③ Age 40 to 79 years old; ④ Patients with clear awareness and good compliance; ⑤ Patients who have signed the informed consent form.

Exclusion criteria: ① Patients with other diseases such as congenital heart disease that cause heart failure; ② Patients complicated with other serious diseases such as malignant tumors; ③ Patients with the presence of other heart lesions such as severe arrhythmia; ④ Patients with severe mental illness.

### Study design

2.5

Subjects meeting inclusion and exclusion criteria will be randomly assigned to control and observation groups in a 1:1 ratio using a central network randomization tool. Random sequences will be generated using SAS 9.3 software (SAS Institute, Cary, NC) by independent statisticians not involved in the treatment process and statistical analysis of the data. Randomization will be performed without any stratification. The clinical study coordinator enters the subject information on a tablet computer and is given a random number. The research assistant gets the subject assignment information from the computer. Throughout the trial, the research assistant is responsible for recruiting, screening, and assigning random numbers to those who have been enrolled in the study. None of the research assistants, intervention supervisors, or those performing statistical analysis are aware of the group assignment.

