### Evaluation criteria and efficacy judgment

2.7

(1)Main outcome indicators: ① Total rate of improvement in cardiac function (refer to the principle of clinical research on treating heart failure with new Chinese Medicine)^[21]^; Excellent: heart failure is essentially ameliorated or the NYHA classification increased by at least 2 levels; Valid: NYHA classification increased by 1 level; Invalid: NYHA classification remain the same before and after the treatment; Worsened: NYHA classification decrease by at least. ② Minnesota Living with Heart Failure Questionnaire,^[13]^ the higher the score, the worse the patient's quality of life.(2)Secondary outcome indicators: left ventricular ejection fraction, N-terminal pro-brain natriuretic peptide, tumor necrosis factor-α, IL- 6, 6-minute walk test.(3)Adverse reactions: including abnormal liver and kidney function and any uncomfortable symptoms (such as dizziness, nausea, etc) during treatment.

The above observation indicators will be collected on the day before and after treatment. All patients will be followed up for 3 months, and data will be collected according to the same criteria in the first and third months.

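### Allocation is unstratified and only unadjusted tests are named, although the first main outcome is movement from baseline NYHA class: valid, but precision is given up at no saving

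*Protocol article*

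**What the plan says.** Section 2.5 of the protocol article has patients "randomly assigned to control and observation groups in a 1:1 ratio using a central network randomization tool", and then fixes that "Randomization will be performed without any stratification". The coordinator enters subject information before the random number is given.

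Section 2.7 names two main outcomes. The first grades each patient by movement in NYHA class between the assessments before and after treatment, for example "Invalid: NYHA classification remain the same before and after the treatment". The second is the Minnesota Living with Heart Failure Questionnaire (MLHFQ). Both are collected before treatment as well as after.

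Section 2.4 admits any ejection fraction below 50% and ages 40 to 79, and sets no limits on NYHA class. Section 2.9 plans chi-square tests for counts and independent-sample t or non-parametric tests for measurements, and names no baseline covariate. Section 2.3 sizes the trial on MLHFQ alone: "34 participants are needed in each group, the estimated withdrawal rate is 10%, so that 38 participants will be included in each group".

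**The concern.** How far a patient can move on the NYHA outcome depends on the class at entry. A class I patient, if enrolled, cannot gain a class, and a class II patient cannot gain two. MLHFQ is itself a measure of disease burden and can be expected to vary with class. Baseline class is therefore likely to be prognostic for both main outcomes.

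The article uses that information neither in the allocation nor in the tests it names. In a trial of 76 patients, two things are at stake. Variation that baseline class could explain stays in the residual error and costs power. And a visible baseline difference between the arms would have no prespecified answer in the named tests, in a trial that already concedes in its Discussion that strict double blinding is not possible.

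**Working it through.** **1. The stated sample size reproduces.** Section 2.3 gives "the observation group will be 27.91 ± 4.31, and the control group will be 31.12 ± 4.85" and "Set α = 0.025, unilateral test, β = 0.20".

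- Difference: 31.12 − 27.91 = 3.21.
- Pooled variance: (4.31² + 4.85²)/2 = 21.05, so SD = 4.588 and standardised difference = 3.21/4.588 = 0.70.
- The normal approximation gives 33 per arm. The exact t calculation gives 34, with power 0.811.
- 34/0.9 = 37.8, rounded up to 38 per arm, or 76 in all.

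**2. Chance imbalance in baseline severity.** Let K of the 76 patients be in the more severe classes. With fixed arms of 38, the number X in one arm is hypergeometric (76, K, 38), and the difference in shares is |2X − K|/38. The documents do not give K, so the share is assumed to lie between 20% and 70%.

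| Assumed severe share | P(difference ≥10 points) | P(≥15 points) | P(≥20 points) |
|---|---|---|---|
| 20% | 0.249 | 0.082 | 0.019 |
| 30% or 70% | 0.318 | 0.133 | 0.045 |
| 40% or 60% | 0.482 | 0.240 | 0.100 |
| 50% | 0.492 | 0.251 | 0.108 |

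The figures jump with whole-number effects: K = 22 gives 0.206 and 0.075 for 15 and 20 points, K = 23 gives 0.133 and 0.045. They are better read as a range than as single values. They are also two-sided, so an imbalance favouring one named arm has half the probability shown.

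**3. Does this damage the unadjusted test?** The improvement rate was simulated with 38 per arm and 40,000 runs per setting. Success was assumed at 80% in milder and 50–60% in more severe patients, and the severe share at 30% or 50%.

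| Unadjusted test | Unstratified | Stratified |
|---|---|---|
| Type I error | 5.0–5.3% | 4.0–4.6% |
| Power, assumed 25-point effect | 66–72% | 67–73% |

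Without stratification the test holds its level. Stratification alone gains about 1 point of power or less, and makes the unadjusted test slightly conservative.

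**4. What adjustment gains on MLHFQ.** If MLHFQ differs by g points between severity groups and a share p is severe, class explains p(1 − p)g² of the within-arm variance of 21.05. The power below uses the remaining SD, 34 per arm, two-sided 5% (equivalent to the stated one-sided 0.025), one degree of freedom for class, and a variance factor of 67/66 for residual chance imbalance.

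| p | g | Variance explained | Remaining SD | Power |
|---|---|---|---|---|
| none | none | 0 | 4.588 | 81.1% |
| 0.2 | 3 | 0.16 × 9 = 1.44 | 4.428 | 83.2% |
| 0.2 | 5 | 0.16 × 25 = 4.00 | 4.129 | 88.0% |
| 0.3 | 3 | 0.21 × 9 = 1.89 | 4.377 | 84.0% |
| 0.3 | 5 | 0.21 × 25 = 5.25 | 3.975 | 90.2% |
| 0.5 | 3 | 0.25 × 9 = 2.25 | 4.336 | 84.7% |
| 0.5 | 5 | 0.25 × 25 = 6.25 | 3.847 | 92.0% |

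A share of 0.7 gives the same values as 0.3. The gain is therefore from about 81% to about 84–91%, with 83–92% as the outer limits over this grid. In simulation, stratifying on top of adjustment adds about 1 point or less. Stratifying without adjustment takes the type I error of the t test down to about 2–4%.

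**The case against.** The strongest case against is that simple 1:1 allocation is a legitimate choice in a single-centre trial, is openly stated, and conflicts with nothing else in the article. That stands.

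A reader might infer that a chance imbalance passes straight into the estimated effect as bias, or that it raises the false-positive rate. The documents do not support this. Imbalance is equally likely to favour either arm. The planning SDs are whole-arm SDs and already contain the spread due to mixed severity, so the standard error allows for it. For scale, a 15-point imbalance with a 5-point gap moves the MLHFQ contrast by 0.15 × 5 = 0.75. The standard error is 4.588 × √(2/38) = 1.05, so this is ordinary sampling variation.

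It is also fair that the severity mix and the MLHFQ gap are assumptions. A gap of 5 points exceeds the within-arm SD and is a strong one, explaining 6.25/21.05 = 30% of the variance at a 50% share. The 50% share likewise gives the largest chance of imbalance. If recruits fall almost wholly in one class, class offers little to adjust for.

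Finally, a separate analysis plan, not shown, could add covariates, and their absence from an article is not in itself a fault. What remains is that the article does name the tests, that they are unadjusted, and that an analysis plan can supply adjustment but cannot alter the allocation.

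**Conclusion.** The point holds as a minor, low-cost improvement. Unstratified allocation with unadjusted tests is valid, but it leaves unused a baseline measure that partly determines the first main outcome and is already collected.

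Over assumed severe shares of 20–70%, an imbalance of 15 points or more has a probability of about 8–25%, and one of 20 points or more about 2–11%. Large imbalances are therefore uncommon. The recoverable precision lies mainly in the analysis: about 81% to about 84–91% power on MLHFQ under assumed gaps of 3–5 points. A smaller gap would give a smaller gain. No claim of bias, of inflated type I error or of an unsound sample size follows.

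**What to change.** In section 2.9, replace the unadjusted chi-square and t tests for the two main outcomes with prespecified adjusted comparisons:

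- **Improvement rate:** compare the arms by a Mantel-Haenszel method stratified by baseline NYHA class, or by logistic regression with class as a factor. The Mantel-Haenszel risk difference keeps the result on the scale of rates. The logistic odds ratio is conditional on class and should be labelled so.
- **MLHFQ:** fit a linear model with treatment, baseline NYHA class and baseline MLHFQ.
- **Grouping of classes:** state in advance how sparse classes will be pooled. Pooling I with II would leave the limit on class I patients unaddressed within that group.

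This costs no patients, visits or new data, only wording and a slightly less simple analysis.

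Optionally, also stratify allocation by baseline class in the central tool, using permuted blocks of varying size. That needs one field entered before the number is issued, a regenerated list before enrolment, and a rule for stratum entry errors. It adds about 1 point of power. It should not be adopted without the adjusted analysis, because the unadjusted test then becomes conservative.

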### Data collection and management

2.8

The data involved in this study will be collected by 2 research assistants, and summarize and analyze by a statistician and a data analyst. Personal information about potential and registered participants will be collected, shared, and kept in a separate storage room to protect confidentiality before and after the trial.

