## Discussion

3

CHD chronic heart failure is characterized by prolonged disease and poor prognosis, which has a serious impact on the quality of life of patients and even endangers their lives. High-quality nursing is the basis to ensure the therapeutic effect.^[22,23]^

Cluster nursing standardizes various nursing processes based on evidence-based evidence, which can reduce the causes of heart failure, reduce the cardiac load of patients, improve the condition of patients, restore the quality of life of patients, and improve the prognosis of patients.^[24,25]^ However, due to few clinical studies on related topics, cluster nursing has not been widely used in clinical nursing of CHD chronic heart failure. Therefore, this study will explore the impact of cluster nursing on the cardiac function and quality of life of CHD patients with chronic heart failure. At the same time, this study has the following limitations: as this is a single-center randomized controlled study, the included population is regionalized, and the results may be biased to some extent; due to the factors of the intervention program, this study could not achieve strict double blindness, which may have some influence on the results.

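### Section 2.5 both gives the research assistant the allocation and says no research assistant knows it, so blind collection of the NYHA-based main outcome and the 6-minute walk is implied but not assured

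*Protocol article*

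**What the plan says.** All places are in the protocol article.

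- **Section 2.5, receipt of the allocation:** "The research assistant gets the subject assignment information from the computer".
- **Section 2.5, next sentence, duties of the role:** "the research assistant is responsible for recruiting, screening, and assigning random numbers to those who have been enrolled in the study". Just before these two sentences, the clinical study coordinator is said to enter the subject on a tablet and be given the random number.
- **Section 2.5, last sentence, blinding:** "None of the research assistants, intervention supervisors, or those performing statistical analysis are aware of the group assignment".
- **Section 2.8, data collection:** "The data involved in this study will be collected by 2 research assistants".
- **Section 2.7, outcomes:** the first main outcome is the "Total rate of improvement in cardiac function", graded mainly by change in NYHA class. The second is the MLHFQ. The 6-minute walk is secondary. The section does not say who grades NYHA class or who runs the walk test.
- **Section 3, limitation:** "this study could not achieve strict double blindness, which may have some influence on the results".

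**The concern.** The blinding sentence covers every research assistant, and the same paragraph hands the allocation to that role. The role also collects the data. If the blinding sentence is taken at its word, the results paper will report outcome collectors as blind. If the sentence on receiving the allocation is taken at its word, at least one person in that role knows the arm.

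This matters most for outcomes that depend on an observer. NYHA class is a judgement, and the top grade in section 2.7 also allows heart failure to count as essentially resolved, for which the article gives no threshold. The result of a walk test can depend on how the patient is encouraged. A collector who knows the arm can shift either without intending to.

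The same sentence also calls intervention supervisors unaware. Section 2.6 describes walking training, posture care, help with expectoration and counselling as the observation group's programme, against routine care in the other arm. The supervisor role is not defined further, but anyone overseeing that care would be expected to recognise the arm.

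**Working it through.** **Step 1. The passages side by side**

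| Question | What the article states | Where |
|---|---|---|
| Who is given the random number? | The clinical study coordinator | 2.5 |
| Who obtains the assignment? | The research assistant | 2.5 |
| Who assigns random numbers? | The research assistant | 2.5 |
| Who is unaware of the group? | All research assistants, intervention supervisors, analysts | 2.5 |
| Who collects the data? | Two research assistants | 2.8 |
| Who grades NYHA class and runs the walk test? | Not stated | 2.7, 2.8 |
| Who is unblinded? | Not stated; only that strict double blinding was not possible | 3 |

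Rows 2 and 4 conflict. The conflict does not depend on which assistant does which task: the blinding sentence admits no exception, so a single assistant who receives an allocation makes it false. Rows 1 and 3 also overlap, because two roles appear to handle the random number.

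**Step 2. Inputs for an illustration of size**

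The contradiction itself needs no arithmetic. The MLHFQ illustration uses the planning values in section 2.3.

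- Means and SDs: 27.91 ± 4.31 and 31.12 ± 4.85. The difference is 31.12 − 27.91 = 3.21.
- Pooled SD = √((4.31² + 4.85²)/2) = 4.588.
- Check of the plan's sample size: the exact t test at one-sided 0.025 has power 0.799 with 33 per group and 0.811 with 34. Then 34/0.9 = 37.8, rounded up to 38. The stated 34 and 38 reproduce.

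**Step 3. NYHA improvement rate (biases assumed, no true effect)**

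Assumptions not in the article: a true improvement rate of 60% in both arms, and a fraction f of non-improved observation patients rated up. The observed rate in the observation arm is 0.60 + 0.40 × f. The test is the two-sided 5% chi-square test without continuity correction, 38 per group, by exact enumeration of the two binomials.

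| f | Observed rates | False-positive rate |
|---|---|---|
| 0 | 0.60 v 0.60 | 0.049 |
| 10% | 0.64 v 0.60 | 0.063 |
| 20% | 0.68 v 0.60 | 0.111 |
| 30% | 0.72 v 0.60 | 0.197 |

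With a continuity correction, the last row falls to 0.130.

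**Step 4. MLHFQ (collector-induced shift assumed, no true effect)**

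Noncentrality = shift / (4.588 × √(2/34)), with 66 degrees of freedom, two-sided 5%. For a 1-point shift this is 1/(4.588 × 0.2425) = 0.899.

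| Shift (points) | False-positive rate |
|---|---|
| 0 | 0.050 |
| 0.5 | 0.073 |
| 1 | 0.144 |
| 1.5 | 0.264 |
| 2 | 0.425 |

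A 1-point shift is 1/3.21 = 31% of the planned difference. These rates apply only to a shift caused by the collector, and the article does not say that a collector administers the questionnaire.

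**The case against.** The strongest reply is that the text does not show that outcomes are collected unblinded. Section 2.5 speaks of one research assistant receiving the assignment, and section 2.8 of two who collect data. Neither says they are the same people, and a split of duties could keep the collectors blind. This stands. A reader might infer that the main outcomes are assessed with knowledge of the arm, and the article does not support that as a fact. It supports only that blinding is not assured. The split is nowhere stated, however, and even with it the sentence claiming that no research assistant knows the group would still be wrong.

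A second reply is that the article never claims blinded outcome assessment in so many words and admits in section 3 that "this study could not achieve strict double blindness". This stands in part. The claim arises by combining sections 2.5 and 2.8, and the limitation is a real but general disclosure. It does not say who is unblinded and does not withdraw the statement about research assistants.

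A third reply is that bias in the MLHFQ comes largely from patients who know their care, and no change to staff access removes it. This stands in full. A reader might take the Step 4 figures as inflation that blinded collectors would prevent; that holds only for a shift caused by how a collector administers the questionnaire.

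Finally, a condensed article may leave detail to the full protocol. That excuses missing detail, but not two statements that conflict.

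**Conclusion.** The contradiction in section 2.5 is certain and rests only on the article's words. Its consequence is that blinding of those who collect the NYHA-based main outcome and the 6-minute walk is implied but not assured, and that the results paper may carry a blinding statement the procedures do not support. The claim about intervention supervisors is implausible, though what that role observes has to be inferred.

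The size of any bias cannot be derived from the article. Under the assumptions shown, the false-positive rate would rise from about 5% to between 6% and 20% for the NYHA rate. For a collector-induced MLHFQ shift of 0.5 to 2 points it would rise to between 7% and 43%. These ranges show sensitivity and are not predictions. It would go too far to conclude that observer bias explains the whole planned effect.

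The point should be settled before enrolment, because outcomes collected with knowledge of the arm cannot be blinded afterwards.

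**What to change.** Reconcile sections 2.5, 2.8 and 3 as follows.

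1. The clinical study coordinator, who already operates the randomisation tool, alone receives the allocation and passes it to the treating nurses.
2. Research assistants have no access to the allocation in the tool. Rewrite the sentence that has them assigning random numbers, so that it agrees with the coordinator's role.
3. The two data-collecting research assistants grade NYHA class and run the 6-minute walk without knowledge of the group.
4. Delete the statement that intervention supervisors are unaware of the group.
5. State that patients and nurses are unblinded, and that outcome collectors and analysts are blinded.
6. Add to the limitations that the MLHFQ is subject to self-report bias from unmasked patients, and that patients may reveal their care to a collector at the assessments after treatment and in months 1 and 3.

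The cost is protocol wording and a change of access rights. The downside is that the coordinator takes over passing on the allocation. The article does not describe staffing, so whether this fits the present workload is for the sponsor to confirm. If the separation cannot be arranged, the alternative is to drop the blinding statement for research assistants and report the NYHA grade and walk test as collected without assured blinding.
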